#### Secondary outcome measure

2.6.2

##### Color doppler ultrasonography^[37]^

2.6.2.1

Color doppler ultrasonography will be performed to calculate the uterine artery blood flow changes by measuring pulsatility index (PI), resistance index (RI) values, and ratio of systolic peak and diastolic peak (S/D ratio). Color doppler ultrasonography will be made by transabdominal type-B ultrasonic diagnostic apparatus LOGIQ E9 XDclear 2.0 (General Electric Co.) with convex probe (3–5 MHz). All participants will be examined at 14:00 to 17:00 with 25°C room temperature in the first day of menstruation by the same specialist. It will be performed at baseline, 5 minutes after needling and 10 minutes after needling (needle removal).

#####  HAM-A

2.6.2.2

The changes of the anxiety will be measured by HAM-A, which is 1 of the first rating scales developed to measure the severity of anxiety symptoms and is widely used in both clinical trial and clinics.^[38]^ It consists of 14 items and measures both psychic and somatic anxiety. Severity of each items will be scored using a 5-point scale ranging from 0 (not present) to 4 (severe). Patients will be assessed with this scale before needling (baseline measurement) and 30 minutes after removing the needles.

##### BP and HR

2.6.2.3

The changes of BP and HR of patients will be measured at baseline, 10 minutes after needling (needle removal) and 30 minutes after removing the needles.

##### Blinding assessment

2.6.2.4

To test whether the participants are blinded successfully, all participants will be asked to guess which kind of acupuncture they received after the treatment.

##### Adverse events

2.6.2.5

All adverse reactions that will be reported by patients and researchers in both groups during the treatment will be recorded in the case report form (CRF).

The schedule of procedures and assessments is presented in Table 1.

**Table 1 T1:**
[figure not shown]
schedule of enrollment, intervention, and assessments.

### Data management and quality control

2.7

The CRF includes observation time points, interventions, outcome measures, and adverse events. The researchers will be required to follow the requirements of the CRF and fill in the relevant information in a timely and accurate manner. The responsible researcher will supervise and monitor the quality of the study. The recruitment and intervention procedures, and record of the CRF will be checked by regular monitoring.

### Statistical analysis

2.8

All statistical analyses will be performed using SPSS 20.0 software (IBM, Armonk, NY) by statistician, who is independent from the research team and blinded to patient allocation. The effects of different needling technique on PD will be analyzed on an intention-to-treat (ITT) approach. To evaluate the sensitivity of analysis, the results of the ITT analysis will be compared with those of per-protocol analysis. Baseline demographic and clinical characteristics of participants will be reported as mean (standard deviation) for continuous variables, and as frequencies (percentages) for categorical variables. Repeated measures analysis of variance (ANOVA) will be used for the analysis of variables, which will be measured at several different times. For other variables, 1-way ANOVA or non-parametric Mann-Whitney *U* test will be applied. Mean differences from baseline to post-treatment in each group will be assessed using paired *t* tests or Wilcoxon signed rank tests. *P* < .05 will be considered significant.

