#### Sample size

2.2.1

In this study, the sample size was calculated according to following repeated measurement formula: 

Where N is the sample size of each groups, α is the significance level (0.05), β is related to study power (0.2) σ^2^ is the variance of measurements, δ is minimum effect size, *p* is the number of observations before treatment of each participant, *r* is the number of observations after treatment of each participant and ρ = 0.65. Based on our previous pilot study^[30]^ with the standard deviation of VAS-P values of 19.67 after 30 minute treatment and minimum clinical effective changes of VAS-P of 10 mm, we calculated that a sample size of 20 per group was a necessary to provide 80% power to detect a difference in the VAS-P value between two groups, considering a 20% drop-out rate, 24 participants are required per group.

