#### Withdraw criteria

2.2.4

Participants could withdraw from the study due to any reason at any time and will not affect the doctor's treatment. Participants who have developed severe adverse events will also withdraw from the study and will be monitored till its resolution.

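### Repeated measures ANOVA, as usually run in SPSS without imputation, drops any woman with one missing VAS-P value, so it does not by itself deliver the promised intention-to-treat analysis

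*Protocol article*

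**What the plan says.** Section 2.8 (Statistical analysis) sets the principle: "The effects of different needling technique on PD will be analyzed on an intention-to-treat (ITT) approach". Its check on robustness is that "the results of the ITT analysis will be compared with those of per-protocol analysis". The method is "Repeated measures analysis of variance (ANOVA) will be used for the analysis of variables, which will be measured at several different times", and the software is fixed: "All statistical analyses will be performed using SPSS 20.0 software (IBM, Armonk, NY) by statistician".

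This covers the primary outcome. Under section 2.6.1, VAS-P is recorded at baseline, at 5 and 10 minutes of needling, and at 10 and 30 minutes after needle removal: one baseline and four later values.

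Two other sections allow for loss. Section 2.2.1 (Sample size) gives the requirement as "a sample size of 20 per group was a necessary to provide 80% power to detect a difference in the VAS-P value between two groups". The enrolment figure then follows from it: "considering a 20% drop-out rate, 24 participants are required per group". Section 2.2.4 (Withdraw criteria) says "Participants could withdraw from the study due to any reason at any time", and adds that women with severe adverse events are also withdrawn.

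The article does not name the SPSS procedure. It does not mention imputation, and it does not say that incomplete cases will be excluded.

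**The concern.** Classical repeated measures ANOVA works on complete vectors. In the usual SPSS procedure for it, a woman who gives four of her five VAS-P values contributes nothing, and the values she did give are discarded. An intention-to-treat analysis is meant to keep randomised women in their assigned arms, so the named method and the stated principle do not fit together unless something further is done with the missing values.

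Three things are at stake:
- **Bias.** The result could be biased if women with incomplete data differ from the others and the loss differs between arms. The article gives some reason to keep this in mind: needling sensation is sought in one arm and avoided in the other (section 2.5), and the Introduction says many patients dislike it.
- **Discarded data.** Observed early pain scores would be thrown away.
- **A weaker robustness check.** If the ANOVA has already removed incomplete cases, the intention-to-treat and per-protocol sets may overlap heavily. Agreement between them would then say little about the effect of drop-out.

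**Working it through.** **Inputs.** From section 2.2.1: SD 19.67 mm, difference 10 mm, correlation 0.65, alpha 0.05 (taken as two-sided, since the article does not say), power 80%, 20 needed per group and 24 enrolled. From section 2.6.1: p = 1 baseline value and r = 4 later values. From the Abstract: 48 randomised 1:1.

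**1. The plan's own sample size.** The formula is not visible in the text at hand. The baseline-adjusted repeated-measures formula is assumed:

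n = 2(z₁₋α/₂ + z₁₋β)² σ²/δ² × [(1 + (r − 1)ρ)/r − pρ²/(1 + (p − 1)ρ)]

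- Bracket with r = 4: (1 + 3 × 0.65)/4 − 0.65² = 0.7375 − 0.4225 = 0.315.
- Leading term: 2 × (1.960 + 0.842)² × 19.67²/10² = 60.74.
- n = 60.74 × 0.315 = 19.13, rounded up to 20. The stated figure is reproduced.
- 20 × 1.2 = 24, the stated enrolment per group.

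**2. Women left out if the whole allowance became missing VAS-P values.**

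- 48 × 0.8 = 38.4 analysed, so 48 − 38.4 = 9.6, or about 10, left out.
- Per group: 24 × 0.8 = 19.2 analysed.

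**3. Power under the same formula (normal approximation).**

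- SD after adjustment: 19.67 × √0.315 = 11.04 mm.
- 24 per group: standard error 11.04 × √(2/24) = 3.19 mm, power 88.1%.
- 19.2 per group: standard error 11.04 × √(2/19.2) = 3.56 mm, power 80.1%.

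Losing the full allowance leaves power at about the planned level, because the enrolment was inflated for it.

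**4. What a partly observed woman is worth.** With three later values in place of four, the bracket is (1 + 2 × 0.65)/3 − 0.4225 = 0.344. The ratio 0.315/0.344 is about 0.92. Under the plan's single correlation, a woman missing only one later value still carries about 92% of her information on the average post-needling score. Complete-row analysis sets that to zero.

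**5. Possible bias (assumptions, not document figures).** Suppose 20% of one arm is lost and none of the other, and the lost women differ from completers in that arm by 5 to 20 mm. The group difference then shifts by 0.2 × 5 = 1 mm to 0.2 × 20 = 4 mm, against a 10 mm target. The article gives no value for either assumption.

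**6. Length of exposure to loss.** Randomisation follows all baseline assessments (section 2.3). Treatment lasts 10 minutes (section 2.5), and the last VAS-P is 30 minutes after needle removal (section 2.6.1). The period is 10 + 30 = 40 minutes, in one visit.

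**The case against.** The strongest objection is that nothing in section 2.8 is contradictory as written. Imputing missing values and then running repeated measures ANOVA on all randomised women would be an intention-to-treat analysis, and SPSS 20 also offers mixed models. The mismatch arises only if the usual procedure is run on unimputed data, and the article fixes neither point. Missing-data rules are commonly left to a full protocol or analysis plan, neither of which is shown. This stands. A reader might infer that the intention-to-treat result will certainly be a completers analysis, but the article does not say so.

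The size is also open to challenge. The 20% is a planning allowance, not a forecast of missing VAS-P values. Women enrol, return at their next period and are treated only if their pain reaches the threshold, so much of any attrition could fall before needling. With some 40 minutes in one visit, a 20% loss after needling is unlikely. Rescue medication does not in itself make a VAS-P value missing. No section says that women with poor relief or needle discomfort would leave early. All of this stands, and it makes the figure of 10 women an upper illustration and the bias mechanism a possibility only.

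Finally, the per-protocol set is not defined. It might also exclude women with complete data who deviated from protocol, so the two sets cannot be called identical.

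What survives is narrower. The method that the article does name does not, on its own, deliver the principle that it states, and a method that handles partial data better is available in the same software.

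**Conclusion.** The point holds in conditional form. Repeated measures ANOVA, as usually run in SPSS and without prior imputation, removes any woman with one missing VAS-P value and so falls short of the promised intention-to-treat analysis. At most, if the full 20% allowance became missing VAS-P values, about 10 of 48 women would be left out. The actual number is probably much smaller.

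A reader might infer that the trial would be underpowered. The figures do not support that: power would be about 80% with 19.2 per group, given the assumed formula, two-sided alpha and the article's SD, difference and correlation. The concern is possible bias of unknown size, discarded observations and a less informative comparison of the two analysis sets. It deserves correction because the remedy costs little. The absence of a missing-data section from a journal article is not itself the fault.

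**What to change.** In section 2.8, replace repeated measures ANOVA for VAS-P with a linear mixed model for repeated measures, fitted in SPSS MIXED by REML. The four post-needling values are the response. Include group, time and group by time, with baseline VAS-P as covariate and an unstructured covariance matrix. Analyse every randomised woman with at least one post-needling value in her assigned arm, and report by arm how many randomised women have none.

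Add one simple sensitivity analysis on all randomised women, with missing values set unfavourably, for example to the woman's own baseline value. Baseline is available because randomisation follows the baseline assessments. This assumes no relief for each affected woman; its effect on the group difference depends on how the losses split between arms. Keep the per-protocol analysis as a separate set.

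The cost is a change of wording, with no new patients, measurements or software. The downside is slightly more analysis work and a covariance model to fit in a small sample: four times give 4 × 5/2 = 10 variance and covariance parameters from at most 48 women.

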#### Primary outcome measure

2.6.1

The severity of dysmenorrhea will be measured by VAS-P, which is continuous quantitative variable varying from 0 mm (no pain) to100 mm (extreme pain). And it has some documented validity and reliability.^[35,36]^ Participants will be assessed by asking to rate the severity of their pain on a standard 100 mm VAS-P at baseline, 5 minutes after needling, 10 minutes after needling (needle removal), and 10 and 30 minutes after removing the needles.

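### The 80% power at 20 per group appears to assume a baseline-adjusted VAS-P comparison, which the stated repeated measures ANOVA does not name; its standard tests have about 32% to 45% power

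*Protocol article*

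**What the plan says.** Section 2.2.1 (Sample size) uses a formula for repeated measurements. Its terms include p, which "is the number of observations before treatment of each participant", and r, which "is the number of observations after treatment of each participant and ρ = 0.65". The variability comes from a pilot study, given as "standard deviation of VAS-P values of 19.67 after 30 minute treatment". The target difference is given as "minimum clinical effective changes of VAS-P of 10 mm". The stated result reads: "a sample size of 20 per group was a necessary to provide 80% power to detect a difference in the VAS-P value between two groups". This is then raised to 24 per group for drop-out.

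Section 2.6.1 schedules the pain ratings as follows: "at baseline, 5 minutes after needling, 10 minutes after needling (needle removal), and 10 and 30 minutes after removing the needles". That is one reading before treatment and four after needling begins.

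Section 2.8 (Statistical analysis) gives one general sentence for all repeatedly measured outcomes: "Repeated measures analysis of variance (ANOVA) will be used for the analysis of variables, which will be measured at several different times". It does not say whether baseline is a level of the time factor, a covariate or neither, nor whether the group effect or the group-by-time interaction decides the trial. Baseline otherwise enters only through paired tests within each group, which do not compare the groups.

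**The concern.** A sample size holds for a particular test. A formula that takes both pre-treatment and post-treatment readings and a correlation gains its precision from how baseline is used. If the analysis uses baseline differently, the power changes, here by a wide margin. VAS-P is the primary outcome, and section 3.5 already gives the small sample as the main limitation. The risk is a trial reported as having 80% power to detect 10 mm when the test actually run had about half that. With no primary effect named, there is also room to choose between the group test and the interaction test after seeing both.

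**Working it through.** **Inputs.** From section 2.2.1: alpha 0.05, power 80%, SD 19.67 mm, difference 10 mm, correlation 0.65. From the VAS-P schedule in section 2.6.1: p = 1 and r = 4. Assumed, because the article does not state them: two-sided alpha, equal variance and equal correlation at all readings (compound symmetry), and a constant 10 mm effect at all four post-baseline readings.

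**Step 1: reproduce the 20 per group.**

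n = 2 × (1.960 + 0.8416)² × 19.67² / 10² × f = 60.74 × f, where f depends on how baseline is used:

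| Form | f | n per group |
|---|---|---|
| Baseline-adjusted (ANCOVA) | (1 + 3 × 0.65)/4 − 0.65² = 0.7375 − 0.4225 = 0.315 | 19.1, so 20 |
| Change from baseline | 0.7375 + 1 − 2 × 0.65 = 0.4375 | 26.6, so 27 |
| Mean of post readings only | 0.7375 | 44.8, so 45 |

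Of these three, only the ANCOVA form returns the protocol's figure.

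**Step 2: power of the tests that a repeated measures ANOVA offers, at 20 evaluable per group.** For one-degree-of-freedom tests, the standard error is 19.67 × √f × √(2/20), and power comes from the noncentral t distribution.

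- *Group effect over all five readings.* The zero difference at baseline dilutes the effect to 4 × 10/5 = 8 mm, and f = (1 + 4 × 0.65)/5 = 0.72. The standard error is 5.28, the ratio 1.52 and the power 31.5%.
- *Group effect over the four post readings, no covariate.* f = 0.7375, standard error 5.34, ratio 1.87, power 44.6%.
- *Group-by-time interaction over five readings, 4 df.* The centred differences are −8, 2, 2, 2, 2, with sum of squares 80. The noncentrality is (20/2) × 80 / (386.9 × 0.35) = 5.91 on F(4, 152), and the power is 45.0%. A linear build-up to 10 mm would give 36%.
- *Change-from-baseline contrast, 1 df, not named in the article.* f = 0.4375, standard error 4.11, ratio 2.43, power 66%.
- *ANCOVA on the post mean.* f = 0.315, standard error 3.49, ratio 2.86, power 79.7%.

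Simulation with 20,000 runs gave 31.0% (five-reading group effect), 44.0% (post-only), 66.1% (change) and 78.2% (ANCOVA).

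**Step 3: the same tests with all 24 per group evaluable.**

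| Test | Power at 20 | Power at 24 | n per group for 80% |
|---|---|---|---|
| Group effect, five readings | 32% | 37% | 69 |
| Group effect, four post readings | 45% | 52% | 45 |
| Group-by-time, 4 df | 45% | 53% | 42 |
| Change contrast, 1 df | 66% | 74% | 27 |
| ANCOVA on post mean | 80% | 87% | 20 |

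**Step 4: two tests, one threshold.** Under compound symmetry the five-reading group test and the interaction test are close to independent. If either were accepted as success at 0.05, the type I error would be about 1 − 0.95² = 9.75%. Power would be about 1 − (1 − 0.315) × (1 − 0.450) = 62% at 20 per group, still below 80%.

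**The case against.** **The formula has not been seen.** Its image is missing from the text, and p, r and sidedness are not given. Section 3.1 calls the trial a noninferiority trial, so a one-sided calculation is conceivable. One-sided ANCOVA with r = 2 also gives 20 (19.3 rounded up). One-sided change score with r = 4 gives 20.9, and so does two-sided ANCOVA with r = 3; both round up to 21. This stands as a limit on certainty. Two-sided ANCOVA with r = 4 fits the schedule and the usual default best, and the one alternative that rounds up to exactly 20 is also baseline-adjusted.

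**Silence is not exclusion.** A reader might infer that the plan rules out baseline adjustment. It does not. Section 2.8 is one general sentence in a condensed article, SPSS repeated-measures models accept covariates, and a full analysis plan may name one. Nor would it be right to say that the ANOVA ignores baseline altogether: with baseline as a time level, the interaction uses it. That test spreads the effect over 4 df, however, and has 45% power. What stands is that the analysis as stated is not shown to be the one the 80% belongs to.

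**Drop-out may be low.** The last VAS-P reading comes 30 minutes after a 10-minute session, so most of the 24 per group could be evaluable. A reader might infer that a true 10 mm difference would more likely be missed than found. At 24 per group two of the three standard tests slightly exceed 50%, so that does not hold generally. All three remain well below 80%.

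**The correlation matters.** At 20 per group, a common correlation of 0.5 gives 37%, 51% and 32% for the five-reading, post-only and interaction tests; at 0.8 the figures are 28%, 40% and 72%. None reaches 80%. At 0.8 with all 24 evaluable, the interaction does reach about 81%, but 0.65 is the protocol's own value.

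**Conclusion.** The point holds as a mismatch between sections 2.2.1 and 2.8. On the protocol's inputs, the 20 per group is best explained by a baseline-adjusted comparison of the mean of four post-baseline readings. The standard tests of the stated ANOVA have about 32% to 45% power at 20 evaluable per group and 37% to 53% at 24. Even the most favourable unadjusted contrast, change from baseline on 1 df, reaches 66% (74%), against 80% (87%) for ANCOVA.

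The figures rest on two-sided alpha, p = 1, r = 4, compound symmetry at 0.65, a common SD of 19.67 mm and a constant 10 mm effect. That the printed formula is the ANCOVA form is an inference.

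Two stronger conclusions are tempting and not supported. One is that the plan doubles its type I error. The rate of about 10% arises only if success on either the group or the interaction test were accepted, and the article states no such rule; it only leaves the choice open. The other is that every secondary outcome needs the same adjustment. The defect shown concerns the power claimed for VAS-P, and the article makes no power claim for the other outcomes.

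**What to change.** In section 2.8, name one primary test for VAS-P: the group contrast averaged over the four post-baseline readings, with baseline VAS-P as covariate, at two-sided 0.05. It can be fitted as ANCOVA on each participant's post-baseline mean or as a linear mixed model on the four readings. Label the time effect, the interaction and the single time points as secondary. If repeated measures ANOVA without the covariate is kept, restate the power in section 2.2.1 for the effect actually tested. In either case, state p, r and sidedness there, and reconcile the primary contrast with the noninferiority description in section 3.1.

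The cost is a short wording change, with the same participants, data and software. The adjusted analysis has one weakness to acknowledge: its 80% depends on the assumed correlation of 0.65, which the 40 mm entry threshold may lower by narrowing the spread of baseline scores. As an illustration, if the baseline-to-post correlation were 0.5 and the post readings still correlated at 0.65, f would be 0.7375 − 0.25 = 0.4875 and n = 60.74 × 0.4875 = 29.6, or 30 per group. Averaging over the four readings is also a choice of estimand, since it includes the readings taken with the needles in place, and should be stated as such.

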### Combination of subjective and objective measures is necessary for pain assessment

3.2

Pain is a complex, multifaceted and subjective experience, which makes a number of measurement challenges. It is important that researchers use sensitive and accurate tools for pain outcome assessments. Currently, there is no valid and reliable method, which objectively quantifies a patient's experience of pain.^[49]^

In the current study, to evaluate subjectively reported symptoms, we will use the VAS-P as the primary outcome measure to assess pain of the patients, and the HAM-A scale also used as secondary outcome. Studies mentioned that women with psychological problems like to have decreased pain thresholds compared to psychologically healthy women. Anxiety and depression affect the patients’ perception of pain, pain behaviors, pain explanation, and also managing response to pain. Therefore, the human's mental health condition could make her susceptible to more severe dysmenorrhea.^[50]^ In addition to subjective assessments by the patients, color doppler ultrasonography will be used to evaluate the uterine artery blood flow changes by measuring PI, RI values, and ratio of S/D ratio. Therefore, we will combine the subjective and objective measures to assess the menstrual pain in the present study.

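### The VAS-P analysis names no baseline covariate, although the sample size reproduces only with baseline VAS-P adjusted for; baseline HAM-A is a cheap second covariate

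*Protocol article*

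**What the plan says.** **Analysis.** Section 2.8 of the protocol article gives one rule that covers the primary outcome: "Repeated measures analysis of variance (ANOVA) will be used for the analysis of variables, which will be measured at several different times". VAS-P falls under it, being rated at baseline and at four times after the needles go in (section 2.6.1). No covariate is named, and adjustment is not ruled out.

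**Sample size.** Section 2.2.1 uses a repeated-measurement formula with terms for the number of readings before and after treatment and for their correlation: "the number of observations after treatment of each participant and ρ = 0.65". The other inputs are a "standard deviation of VAS-P values of 19.67 after 30 minute treatment" and, for the difference to be detected, "minimum clinical effective changes of VAS-P of 10 mm". The result reads: "a sample size of 20 per group was a necessary to provide 80% power to detect a difference in the VAS-P value between two groups". This is then raised to 24 per group for drop-out.

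**Anxiety.** Section 3.2 explains the use of HAM-A by saying that anxiety and depression affect patients' "perception of pain, pain behaviors, pain explanation, and also managing response to pain". On timing, section 2.6.2.2 says: "Patients will be assessed with this scale before needling (baseline measurement) and 30 minutes after removing the needles". HAM-A appears throughout as a secondary outcome and nowhere as a covariate.

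**The concern.** Two statements in the article point to a baseline-adjusted analysis of VAS-P that section 2.8 does not name.

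The first is the sample size. A formula that takes the number of pre-treatment readings and their correlation with later ones can credit the trial with the variance that baseline pain removes. If 20 per group relies on that credit and the analysis does not adjust for baseline, the trial has less power than stated.

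The second is the article's own view that anxiety shapes pain. A score taken before needling cannot be affected by treatment, so it may serve as a covariate as well as an outcome. In a trial whose main limitation, by its own account (section 3.5), is small size, variance that could be removed at no data cost deserves attention.

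What is at stake is precision and power, not the validity of the comparison.

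**Working it through.** **Inputs.** From section 2.2.1: SD 19.67 mm, difference 10 mm, ρ = 0.65, α = 0.05 (sidedness not stated; two-sided taken), power 80%. From the schedule in section 2.6.1, not stated as values in 2.2.1: p = 1 reading before and r = 4 after. The formula itself is not visible in the text at hand, so its form is inferred from which version returns 20.

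**Step 1: reproduce 20 per group.** With one post-treatment value and no adjustment,

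n = 2 × (1.960 + 0.842)² × (19.67/10)² = 2 × 7.849 × 3.869 = 60.74.

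Each form of the analysis multiplies this by a variance factor:

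| Analysis | Factor | n per group |
|---|---|---|
| Single post value | 1 | 60.74, so 61 |
| Mean of 4 post values | (1 + 3 × 0.65)/4 = 0.7375 | 44.79, so 45 |
| Mean post minus baseline | 0.7375 + 1 − 2 × 0.65 = 0.4375 | 26.57, so 27 |
| Mean post, adjusted for baseline | 0.7375 − 0.65² = 0.315 | 19.13, so 20 |

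One-sided α = 0.05 gives 15.07 (16) for the adjusted form and 15.07 × 0.4375/0.315 = 20.93 (21) for the change form. Of these, only the two-sided baseline-adjusted form gives 20.

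**Step 2: power at 20 per group.** The standard error is 19.67 × √(2 × factor/20).

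- Baseline-adjusted: SE 3.49 mm; Φ(10/3.49 − 1.96) = 81.7%. The t distribution gives 79.7%, and 78.6% once the covariate is estimated and chance imbalance in it is allowed for; about 79%.
- Change from baseline: SE 4.11 mm; 68.1% by the normal approximation, 65.9% by the t distribution; about 66%.
- Mean of post values alone: SE 5.34 mm; 46.5% (normal), 44.6% (t).

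Baseline VAS-P is therefore worth about 13 points of power against a change contrast.

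**Step 3: what HAM-A adds.** Let R be the partial correlation of baseline HAM-A with mean post-needling VAS-P, given baseline VAS-P. The article gives no value, so R is an assumption. The residual SD after baseline VAS-P is 19.67 × √0.315 = 11.04 mm, and HAM-A multiplies it by √(1 − R²). Power is t-based at 20 per group (37 degrees of freedom without HAM-A, 36 with), averaged over simulated covariate imbalance:

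| R | Without HAM-A | With HAM-A | Change (points) |
|---|---|---|---|
| 0 | 78.6% | 77.4% | −1.2 |
| 0.15 | 78.6% | 78.3% | −0.3 |
| 0.2 | 78.6% | 79.0% | +0.5 |
| 0.3 | 78.6% | 81.1% | +2.5 |
| 0.4 | 78.6% | 84.1% | +5.5 |

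The normal approximation (81.7% at R = 0, 83.2% at 0.2, 85.1% at 0.3, 87.8% at 0.4) hides the cost at R = 0, because it ignores the lost degree of freedom and chance imbalance.

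**Step 4: chance imbalance.** At 24 per arm the between-arm difference in standardised HAM-A has SD √(2/24) = 0.289 and exceeds 0.5 in 8.3% of randomisations. With R = 0.3, a 0.5 SD imbalance moves the estimate by 0.3 × 0.5 × 11.04 = 1.7 mm; a typical one of 0.289 SD moves it by 1.0 mm. The standard error of the baseline-adjusted difference, 11.04 × 0.289 = 3.2 mm, already contains this variation.

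**The case against.** The strongest reply is that a condensed article commonly leaves the covariate list to a statistical analysis plan, which is not at hand, and that section 2.8 does not exclude adjustment. This stands as far as silence goes: the article cannot be said to forbid baseline adjustment. It does not remove the mismatch between a sample size that credits baseline VAS-P and a named method that mentions no such covariate.

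On HAM-A the reply is stronger. Using anxiety as a secondary outcome is coherent, and nothing obliges an outcome to be a covariate too. Section 3.2 makes a general statement about anxiety and pain; it does not show that baseline HAM-A predicts VAS-P beyond baseline VAS-P. That increment may be small: severe and uncontrolled psychiatric disorders are excluded, treatment requires a VAS-P of at least 40 mm, and HAM-A's somatic items may overlap with pain. No stated figure depends on HAM-A. All of this stands.

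A reader might infer more in three ways, none of them supported:

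- That omitting HAM-A biases the result through chance imbalance. Under 1:1 randomisation it does not; the imbalance is part of the standard error.
- That randomisation should have been stratified by anxiety. Nothing in the article requires this for a 48-patient trial and a continuous score.
- That the planned test is known to be badly underpowered. Section 2.8 does not say which effect of the repeated measures ANOVA is tested, so the 66% describes one plausible contrast, not the plan's established power.

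**Conclusion.** The point holds as a low-severity improvement, not as an error. Its larger part is baseline VAS-P: the article's 20 per group is recovered (19.13) only by adjusting for it, and power at 20 per group is about 79% with that adjustment against about 66% for a change-from-baseline contrast. This rests on p = 1 and r = 4 read from the schedule, two-sided α, equal correlation of 0.65 between readings, and a constant 10 mm difference at all four post-needling times.

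The smaller part is HAM-A. Adding it costs 1.2 to 1.3 points of power if it is unrelated to pain given baseline VAS-P, breaks even at a partial correlation of roughly 0.15 to 0.2, and gains about 3 points at 0.3 and about 6 at 0.4. The article supports the direction of the relation, not its size, so the gain cannot be fixed from the document.

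**What to change.** In section 2.8, or in the analysis plan before unblinding, name the primary VAS-P model: a repeated measures model for the four post-needling values, with baseline VAS-P as covariate and the between-group difference over those four times as the contrast. This matches the calculation that yields 20 per group. Add baseline HAM-A total as a second pre-specified covariate, kept whatever the observed balance, and report the model without HAM-A as a sensitivity analysis.

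The change takes one or two sentences and no new data, since both scores are already collected before needling. The price of HAM-A is one degree of freedom and, if it proves unrelated to pain, a little over 1 point of power. Fixing the choice in advance also prevents a decision about adjustment after imbalance has been seen.
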